## Abstract

**Background:**

Verrucae are a common, infectious and sometimes painful problem. The optimal treatment for verrucae is unclear due to a lack of high quality randomised controlled trials. The primary objective of this study is to compare the clinical effectiveness of two common treatments for verrucae: cryotherapy using liquid nitrogen versus salicylic acid. Secondary objectives include a comparison of the cost-effectiveness of the treatments, and an investigation of time to clearance of verrucae, recurrence/clearance of verrucae at six months, patient satisfaction with treatment, pain associated with treatment, and use of painkillers for the treatments.

**Methods/Design:**

This is an open, pragmatic, multicentre, randomised controlled trial with two parallel groups: cryotherapy using liquid nitrogen delivered by a healthcare professional for a maximum of 4 treatments (treatments 2-3 weeks apart) or daily self-treatment with 50% salicylic acid for a maximum of 8 weeks. Two hundred and sixty-six patients aged 12 years and over with a verruca are being enrolled into the study. The primary outcome is complete clearance of all verrucae as observed on digital photographs taken at 12 weeks compared with baseline and assessed by an independent healthcare professional. Secondary outcomes include self-reported time to clearance of verrucae, self-reported clearance of verrucae at 6 months, cost-effectiveness of the treatments compared to one another, and patient acceptability of both treatments including possible side effects such as pain. The primary analysis will be intention to treat. It is planned that recruitment will be completed by December 2009 and results will be available by June 2010.

**Trial registration:**

Current Controlled Trials ISRCTN18994246.

## Background

Verrucae or plantar warts are a common, infectious and sometimes painful problem. Although most verrucae will spontaneously disappear without treatment many patients seek treatment to remove a verruca due to it being painful or because they are being prevented from doing sports and other activities of daily living. Two common treatments for verrucae are cryotherapy using liquid nitrogen which involves freezing the tissues at below -60C or application of a salicylic acid paste which macerates the skin. Using incidence figures from the 4th National Morbidity Survey [1], an economic decision model assessing the effectiveness and cost-effectiveness of salicylic acid and cryotherapy has estimated that almost 2 million people in England and Wales see their General Practitioner (GP) per year about cutaneous warts at a cost of at least £40 million per annum [2].

A systematic review conducted by the Cochrane Skin Group assessed the effects of different local treatments of cutaneous, non-genital warts in healthy people [3]. This review highlighted the uncertainty with respect to the optimal treatment of verrucae. There was, however, some evidence from six trials to suggest that treatment with salicylic acid was more effective than placebo/no treatment, odds ratio 3.91 (95% confidence interval (CI) 2.40 to 6.36). Many patients experience unpleasant side effects such as pain and blistering during cryotherapy treatment, yet the same review found no evidence to suggest that it is more effective than treatment with topical agents such as salicylic acid. Only two trials were identified which compared salicylic acid and/or lactic acid with cryotherapy, and they found no difference in the efficacy between the treatments (odds ratio 1.15, 95% CI 0.72 to 1.82). However, both trials were reported as low quality, due to unclear allocation concealment, inadequate blinding procedures, small sample sizes and inappropriate follow-up and analysis. There is a need, therefore, for a high quality randomised controlled trial with a cost-effectiveness analysis to ascertain which is the better approach for the treatment of verrucae.

The primary objective of the EVERT trial is to compare the clinical effectiveness of cryotherapy versus salicylic acid for the treatment of verrucae. Secondary objectives are to compare the cost-effectiveness of cryotherapy versus salicylic acid, and to investigate time to clearance of verrucae, recurrence/clearance of verrucae at six months, patient satisfaction with treatment, pain associated with treatment, and use of painkillers for the two treatments.

## Methods

### Design

This is an open, pragmatic, two-arm, multicentre, randomised controlled trial. Patients with verrucae are randomised equally to cryotherapy using liquid nitrogen delivered by a healthcare professional (a podiatrist, practice nurse or GP) or once daily self-treatment with 50% salicylic acid paste (Verrugon; William Ransom & Son Plc, Hitchin, UK). Two hundred and sixty-six patients are being enrolled into the study at recruiting sites in the UK and Southern Ireland for a period of 24 weeks, with treatment lasting a maximum of 8 or 9 weeks. The primary outcome is assessed at 12 weeks. Recruitment started in October 2006 and will continue until approximately December 2009. The study has been approved by the Trent Multi-centre Research Ethics Committee (Reference Number 04/mre04/59), the Medicines and Healthcare Products Regulatory Agency (MHRA), The Irish Medicines Board (IMB) and the ethics or National Health Service (NHS) research and development committee responsible for each site. The study is being conducted in accordance with the ethical principles in the Declaration of Helsinki and good practice guidelines on the proper conduct of research.

### Participants

Patients are eligible if they (i) have a verruca that in the opinion of the healthcare professional is suitable for treatment with both salicylic acid and cryotherapy and (ii) are aged 12 years and over. Patients are excluded if they (i) are currently in a trial evaluating other treatments for their verruca, (ii) have impaired healing e.g. due to diabetes, peripheral vascular disease or any other condition which means the patient has impaired healing, (iii) are immunosuppressed e.g. have agammaglobulinaemia, or are currently taking immunosuppressant drugs such as oral corticosteroids, (iv) are unable to give informed consent, (v) are currently on renal dialysis, (vi) have cold intolerance e.g. Raynaud's syndrome or cold urticaria, or (vii) have any of the following conditions: blood dyscrasias of unknown origin, cryoglobulinaemia, cryofibrinogenaemia, collagen and auto-immune disease.

Recruitment is taking place in both podiatry outpatient clinics (hospital-based or university podiatry school-based) and general practice at eight recruiting sites in the UK and one in Southern Ireland. To aid recruitment, a number of strategies have been adopted to increase the number of patients presenting to the clinics and GP practices e.g. the trial has been advertised at pharmacies, GP surgery waiting rooms, swimming pools, libraries and secondary schools local to the recruiting sites.

All patients, and their parent/guardian for patients under the age of 16 years, are given written information about the study and opportunity to discuss the study with the trial coordinator and/or site investigator prior to their decision whether to take part. Written informed consent is obtained from the patient, or the parent/guardian for those under 16 years, prior to being randomised. The healthcare professional at the recruiting site randomises the patient using the remote, independent York Trials Unit (University of York, UK) telephone or web-based randomisation service. Randomisation is simple, that is it is not restricted in any way, for example by stratification or blocked allocation. The allocation sequence is computer generated, with the treatment allocation being concealed from both the healthcare professional and York Trials Unit until the moment of randomisation.

### Interventions

For patients randomised to cryotherapy using liquid nitrogen, treatment is delivered by the healthcare professional according to the usual practice of each trial site. Prior to treatment, the callus surrounding the verruca(e) may be debrided (e.g. with a scalpel or file) with any haemorrhages stopped by digital pressure only. The tissue surrounding the verruca may be masked (e.g. with petroleum jelly) or left unmasked. Liquid nitrogen is then applied using a spray (method of choice if available), probe or cotton bud, until the healthcare professional is satisfied that the tissue has been frozen adequately. Silver nitrate may not be applied to the site. If necessary, after treatment the healthcare professional may pad the area surrounding the verruca e.g. with 7 mm felt cavitied padding. The patient is recommended to use painkillers as they would for a headache if the area is very painful. All patients are given a follow-up appointment at 2 weeks as a safety check and for further cryotherapy if considered necessary. Patients return up to two more times for further cryotherapy if required (up to a maximum of four treatments), with 14 to 21 days between treatments. All participants are given a follow-up appointment at 12 weeks for the primary outcome assessment.

Patients randomised to self-treatment with 50% salicylic acid are instructed by the healthcare professional how to use the salicylic acid paste at the first trial appointment. Thereafter, the acid paste is applied daily by the patient (or parent/guardian if appropriate) for a maximum of 8 weeks as per the manufacturer's instructions. All patients are given a follow-up appointment at 2 weeks as a safety check and at 12 weeks for the primary outcome assessment.

### Study evaluations

#### Primary outcome

The primary outcome is complete clearance of all verrucae at 12 weeks as observed on digital photographs taken by the healthcare professional delivering the treatment at baseline and 12 weeks and assessed by an independent healthcare professional. Blinded healthcare professional assessment of clearance is also performed at the 12 week appointment, to be used if for some reason the digital photograph is not interpretable. Clearance of verrucae is defined as the restoration of normal skin upon close inspection, as assessed by the healthcare professional. Participants who do not attend their 12 week outcome assessment appointment are asked if they are willing to take a digital photograph of their foot.

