#### Sample size

The Cochrane systematic review [3] found only one small trial directly comparing the effectiveness of a chemical treatment, salicylic acid, with cryotherapy in patients with warts on their feet alone [4]. This poor quality study found a 58% cure rate among the patients allocated to cryotherapy compared with 41% among those treated with salicylic acid. This difference of 17% was not statistically significant. The overall cure rates from this study are smaller than those observed in two placebo controlled trials of salicylic acid, both of which reported cure rates of 85% for active treatment, possibly because more resistant verrucae were included in the study comparing cryotherapy with salicylic acid. The EVERT trial is powered to show a 15% difference in effectiveness. Sufficient patients will be recruited to give 80% power (5% two sided significance) to show a difference in cure rates of 70% versus 85% at 12 weeks. This requires 120 patients in each group; after allowing for a 10% drop-out rate, 133 will be required in each treatment group (i.e. 266 in total).

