### Statistical analysis

Data on baseline demographics such as gender, age, type and duration of verrucae, and previous treatments will be summarised and descriptive summary statistics provided. For variables with continuous measures we will report the mean and standard deviation. For categorical data we will report numbers and percent.

Analysis will be by 'intention to treat'. All patients will be included in their initially randomised groups whether or not they received their allocated treatment. Analyses will be conducted blind to group. There will be a single primary analysis at the end of the study using 5% two sided significance tests. The primary outcome is complete clearance of all verrucae at 12 weeks. The two treatment groups will be compared using simple proportions of cure or not cured using the Chi squared test.

For the secondary outcomes stricter statistical levels of significance will be adopted (i.e. p = 0.01) to reduce the chance of type I error. Survival analysis of patient self-reported time to clearance of verrucae, censoring for loss to follow up, will be tested for using Cox regression adjusting for relevant co-variates to be defined before the analysis. The recurrence/clearance of verrucae at 6 months will be analysed in the same way as the primary outcome measure. The primary analysis will be repeated, but controlling for age, whether or not the verruca has been previously treated and type of verruca. Should numbers be sufficient, in order to examine whether mosaic verrucae respond less well to treatment than simple verrucae, the primary analysis will be repeated, but the type of verruca mosaic/simple will be included as a covariate and also an interaction term verruca type*treatment will be included [5]. As patients and healthcare professionals are not blinded to treatment, we will carry out a second, sub group analysis, assessing the influence of participant's treatment preference on treatment outcomes and the results of the cost-effectiveness analysis.

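### The 12-week photograph that decides the primary outcome is taken by the unblinded treating professional, although a blinded professional assesses the patient at the same appointment

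*Protocol article*

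**What the plan says.** All references are to the Protocol article.

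- **Who takes and reads the image (Primary outcome).** Complete clearance at 12 weeks is judged on "digital photographs taken by the healthcare professional delivering the treatment at baseline and 12 weeks and assessed by an independent healthcare professional".
- **Who knows the allocation.** Design: "This is an open, pragmatic, two-arm, multicentre, randomised controlled trial". Statistical analysis: "As patients and healthcare professionals are not blinded to treatment".
- **What else happens at week 12 (Primary outcome).** "Blinded healthcare professional assessment of clearance is also performed at the 12 week appointment". Its role is that of a back-up, "to be used if for some reason the digital photograph is not interpretable".
- **What counts as cleared (Primary outcome).** "Clearance of verrucae is defined as the restoration of normal skin upon close inspection, as assessed by the healthcare professional".
- **Missed visits (Primary outcome).** "Participants who do not attend their 12 week outcome assessment appointment are asked if they are willing to take a digital photograph of their foot".

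The abstract adds that the 12-week photographs are compared with baseline.

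**The concern.** Independent reading protects the reading step only. The reader sees what the photographer recorded, and the photographer at week 12 is someone who knows the allocation and gave or taught the treatment. There are two ways in which that knowledge could reach the primary outcome:

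1. **Acquisition.** Clearance must hold for every verruca and is defined by close inspection. Whether a small residual lesion shows in an image depends on framing, focus and light.
2. **Source of the outcome.** Image quality decides whether a photograph can be interpreted, and so whether the photograph or the blinded in-person assessment supplies that patient's result. The safeguard is triggered by the step it is meant to guard.

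The exposure is avoidable, because someone unaware of allocation already assesses the patient at that appointment. The economic analysis takes its effectiveness measure from the same outcome and would carry any error forward.

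**Working it through.** **Step 1. Reading the text.** The phrase about baseline and 12 weeks must say when photographs are taken, not when treatment is given: Design puts the end of treatment at 8 or 9 weeks at the latest. So the treating professional takes the week-12 image. In the salicylic acid arm patients treat themselves, so the corresponding person is the professional who gave the instruction and who also knows the allocation. The statement that professionals are unblinded and the statement that one is blinded are compatible if the first means treating staff and the second means the 12-week assessor. No section has the blinded assessor take the photograph.

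**Step 2. The plan's own figure.** Inputs from Sample size: 70% versus 85%, two-sided 5%, 80% power. With pooled variance under the null and mean rate 0.775:

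n = [1.96 × √(2 × 0.775 × 0.225) + 0.8416 × √(0.70 × 0.30 + 0.85 × 0.15)]² / 0.15² = 120.5 per group.

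The plan states 120, for which power is 79.8%. The figure is reproduced, and who holds the camera does not change it.

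**Step 3. Size of a possible shift (assumption).** The documents give no bias size. Suppose residual lesion is concealed in a fraction f of uncleared patients in one arm only, with f = 5% to 10%. Shift = (1 − cure rate) × f.

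| Arm affected | Uncleared | f = 5% | f = 10% |
|---|---|---|---|
| Cure rate 70% | 30% | 1.5 points | 3 points |
| Cure rate 85% | 15% | 0.75 points | 1.5 points |

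The range is 0.75 to 3 points. Against the 15-point target this is 0.75/15 = 5% to 3/15 = 20%.

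**Step 4. What such a shift would do.** With 120 per group, an uncorrected chi-squared test and the normal approximation:

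| Scenario | Observed rates | Probability of a significant result |
|---|---|---|
| True 70% v 85%, no shift | 70% v 85% | 79.8% |
| True 70% v 85%, lower arm raised 1.5 points | 71.5% v 85% | 72.0% |
| True 70% v 85%, lower arm raised 3 points | 73% v 85% | 62.8% |
| Equal at 70%, one arm raised 1.5 points | 70% v 71.5% | 5.7% |
| Equal at 70%, one arm raised 3 points | 70% v 73% | 8.1% |
| Equal at 85%, one arm raised 0.75 points | 85% v 85.75% | 5.3% |
| Equal at 85%, one arm raised 1.5 points | 85% v 86.5% | 6.3% |

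Exact binomial calculation agrees to within one percentage point throughout. If the higher arm were the one raised, the true difference would be exaggerated instead. The documents do not indicate a direction.

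**The case against.** The case on the other side is substantial, and much of it stands.

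- **Existing protection.** The reader is independent, the image is compared with baseline so lesion sites are known, and a poor image is replaced by a blinded in-person result. A site left out of frame would probably be noticed. What remains is an image that looks adequate but hides residual lesion, plus some influence on which images fail. This is narrower than unblinded assessment, and a reader who infers that the primary outcome is assessed unblinded goes beyond the text.
- **Possible inferences about conduct.** One might suppose that the photographer chooses which frames to submit or prepares the skin at week 12. The article says neither. The absence of a standard view is no finding either, since camera instructions may sit in the full protocol. Nor does calling the reader independent rather than blinded show that the reader knows the allocation.
- **One-arm assumption.** Nothing in the article shows that photographers favour one treatment. Influence common to both arms would move the difference much less.
- **Correctable in analysis?** A reader might infer that the damage could not be repaired afterwards. That is not so for attenders: the blinded in-person assessment is already performed at the visit and does not depend on the photograph. The unseen analysis plan may already use it as a sensitivity analysis.

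None of this removes the point itself. The article states who takes the deciding image, and that person is unblinded when a blinded colleague could do it.

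**Conclusion.** The concern holds as an avoidable exposure to bias, not as a demonstrated bias, a miscalculation or a contradiction. Knowledge of allocation can enter through image acquisition and through the route to the back-up assessment. Its size cannot be derived from the documents. Under the stated one-arm assumption it is 0.75 to 3 points, or 5-20% of the target difference: small at the lower end and material to power at the upper end. Larger shifts would do more harm, but nothing in the article supports assuming them. The change is worth making because it is cheap, not because the effect is known to be large.

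**What to change.** 1. **Remaining patients.** Amend Primary outcome so that the 12-week photograph is taken by the blinded professional who performs the 12-week assessment.
2. **All attenders, including those already photographed.** Repeat the primary analysis using the blinded in-person assessment for everyone who attended, not only where the photograph failed. Some disagreement with the photograph-based result is to be expected from the two methods themselves, so a difference between the analyses would be a warning rather than proof of bias.
3. **Reporting.** Give the number and proportion of uninterpretable photographs by arm.

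**Cost.** No extra visit, no extra staff role and no change to the sample size. Items 2 and 3 use data already being collected. Item 1 needs a wording change across nine sites, with whatever approvals that requires, and brief camera training. It assumes that the blinded professional at each site can take on photography, which the article does not say. Recruitment began in October 2006, so the photographer would change partway through. Photographs that participants take themselves after a missed visit are not covered.

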#### Secondary outcomes

Secondary outcomes are time to clearance of verrucae, clearance of verrucae at six months, pain intensity of the first treatment (on a scale of 0 to 10, where 0 is no pain and 10 is the worst pain imaginable), use of painkillers due to verruca treatment (number of days painkillers taken), and patient satisfaction with the treatment (on a 5 point scale, from 'very unhappy' to 'very happy'). All secondary outcome measures are self-reported by the patient and assessed by questionnaire (either paper or web-based according to the patient's preference), which patients are requested to complete at baseline, just after the first treatment and at 1, 3, 12 and 24 weeks. Patients are supplied with a form to return to York Trials Unit when their verruca has gone.

For the economic evaluation, data on the number of visits to healthcare professionals in relation to verruca treatment (trial investigator and any other) and cost of other verruca treatments purchased by the patient are collected in the 12 week questionnaire completed by the patient and from clinic records of attendance.

#### Further data collected

Other data collected in the questionnaires completed by the patients include pain associated with the verrucae (on a 5 point scale, from 'not at all' to 'extremely'), number of days over a two week period the patient has self-treated with salicylic acid, reasons for seeking treatment for the verruca(e), how long the patient has had the verruca(e), whether they received previous treatment for the verruca(e), willingness to receive the same treatment again if they had another verruca, if the patient had to stop treatment, reasons for this and whether they started another treatment, number of previous verrucae and age at which they occurred. Treatment details for both groups, number and type of verrucae and participant's treatment preference are collected via a questionnaire completed by the healthcare professional. Data on adverse events, self-reported by the patient (verbally and/or by questionnaire) or elicited by the healthcare professional following questioning of the patient at each study visit, are collected.

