Data on side effects and pain intensity during and after treatment, use of painkillers, reasons for seeking treatment for the verruca, treatment details, patient satisfaction with treatment and number of verrucae, will be summarised and descriptive summary statistics provided. The number of patients discontinuing treatment prematurely for any reason will be summarised by treatment group and by reasons for discontinuation. The incidence of all suspected adverse treatment reactions will be summarised by treatment group.

For each outcome measure, the number of non-responders (missing data) will be calculated for each treatment group. We shall compare at each follow-up point the number and proportion of non-responders in each group and the type of non-responder e.g. proportion of males not responding in each group. Appropriate methods for dealing with missing data will be employed and sensitivity analyses performed.

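### Questioning about adverse events is tied to visits, and cryotherapy has 3 to 5 visits against 3 for acid, so the by-arm table of suspected reactions leans, probably modestly, against cryotherapy.

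*Protocol article*

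**What the plan says.** Under Further data collected, the protocol article names two channels for adverse events. The first is self-report: "Data on adverse events, self-reported by the patient (verbally and/or by questionnaire"). The second is active questioning, with events "elicited by the healthcare professional following questioning of the patient at each study visit".

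The Interventions section sets a different visit schedule for each arm.

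- **Cryotherapy:** a first treatment visit, then "All patients are given a follow-up appointment at 2 weeks as a safety check and for further cryotherapy if considered necessary". After that, "Patients return up to two more times for further cryotherapy if required (up to a maximum of four treatments"). Successive treatments are spaced 14 to 21 days apart. Finally, "All participants are given a follow-up appointment at 12 weeks for the primary outcome assessment".
- **Salicylic acid:** a first appointment for instruction, then "All patients are given a follow-up appointment at 2 weeks as a safety check and at 12 weeks for the primary outcome assessment". The paste is applied at home each day for at most 8 weeks.

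The patient questionnaires follow one schedule for both arms (Secondary outcomes), "which patients are requested to complete at baseline, just after the first treatment and at 1, 3, 12 and 24 weeks".

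The Statistical analysis section then plans a descriptive summary: "The incidence of all suspected adverse treatment reactions will be summarised by treatment group". It does not mention the source of an event or the unequal number of visits.

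**The concern.** A reaction enters the table only if someone records it. One of the two recording channels operates at visits, and the number of visits depends on the arm. With identical true rates, the arm questioned more often will show more reactions.

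The shared questionnaires do not close the gap, because none is due between weeks 3 and 12. The third and fourth cryotherapy visits fall inside that interval. In the same weeks an acid patient may still be applying paste daily but has no scheduled contact of either kind until week 12. A mild acid reaction at week 5 that has settled must be recalled some seven weeks later. A cryotherapy patient with further treatments due would be asked within two to three weeks.

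This matters because the Abstract counts acceptability and side effects among the secondary outcomes, and the Background cites unpleasant side effects of cryotherapy. If clearance turns out similar, readers will look to tolerability. The ascertainment difference pushes that table in the direction the Background already leads them to expect.

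**Working it through.** **Visit counts (Interventions).** The plan's own figure comes out first: cryotherapy treatments = first visit 1 + week 2 visit 1 + up to 2 more = 4, the stated maximum.

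| | Cryotherapy | Acid |
|---|---|---|
| All visits | 1 + 1 + (0 to 2) + 1 = 3 to 5 | 1 + 1 + 1 = 3 |
| After baseline | 2 to 4 | 2 |
| After week 2 | 1 to 3 | 1 |

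**Timing.** From week 2, with 2 to 3 weeks between treatments, the third treatment falls at about week 4 to 5 (2 + 2 to 2 + 3). The fourth falls at about week 6 to 8 (4 + 2 to 5 + 3). Both lie between the week 3 and week 12 questionnaires.

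**Size.** The document gives no capture rates, so these are assumptions:
- q is the chance that questioning at one visit picks up a reaction (0.3, 0.5 or 0.8).
- s is the chance that self-report picks it up, taken as equal in both arms.
- m is the number of visits after the reaction.
- Channels and visits act independently, and true incidence is equal in the two arms.

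Share of true reactions recorded = 1 − (1 − s)(1 − q)^m.

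For a reaction after week 2 that precedes both extra visits, m = 3 for cryotherapy and m = 1 for acid:

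| s | q | Cryotherapy | Acid | Ratio |
|---|---|---|---|---|
| 0.5 | 0.3 | 1 − 0.5×0.343 = 0.829 | 1 − 0.5×0.7 = 0.650 | 1.27 |
| 0.5 | 0.5 | 1 − 0.5×0.125 = 0.938 | 1 − 0.5×0.5 = 0.750 | 1.25 |
| 0.5 | 0.8 | 1 − 0.5×0.008 = 0.996 | 1 − 0.5×0.2 = 0.900 | 1.11 |
| 0.8 | 0.3 | 1 − 0.2×0.343 = 0.931 | 1 − 0.2×0.7 = 0.860 | 1.08 |
| 0.8 | 0.5 | 1 − 0.2×0.125 = 0.975 | 1 − 0.2×0.5 = 0.900 | 1.08 |
| 0.8 | 0.8 | 1 − 0.2×0.008 = 0.998 | 1 − 0.2×0.2 = 0.960 | 1.04 |

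In absolute terms, with an assumed true incidence of 20% and s = q = 0.5, acid would show 0.20 × 0.750 = 15.0% and cryotherapy 0.20 × 0.9375 = 18.8%.

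**Variations.**
- One extra visit after the reaction (m = 2 v 1), s = q = 0.5: (1 − 0.5×0.25)/0.75 = 1.17.
- No extra visit after the reaction (m = 1 v 1): 1.00.
- All visits after baseline at the full schedule (m = 4 v 2): 1.02 to 1.17 with s = 0.5, and 1.01 to 1.06 with s = 0.8.
- Self-report capturing nothing (s = 0, m = 3 v 1): 0.657/0.3 = 2.19, 0.875/0.5 = 1.75 and 0.992/0.8 = 1.24 for q = 0.3, 0.5 and 0.8. This is a bound, not an estimate.

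**The case against.** Five points can be made for the plan.

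1. *Self-report is a named channel and its questionnaires are common to both arms.* This stands and limits the size. A reader might infer from the visit counts that cryotherapy reactions could be over-reported about twofold. The document does not support that, because such ratios need self-report to capture nothing and every extra visit to follow the reaction.

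2. *Five visits is a maximum.* This also stands. Further visits occur only if required. A reaction to the fourth treatment has only the week 12 visit after it, as in the acid arm.

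3. *The tolerability outcomes are largely protected.* A reader might conclude that the whole tolerability comparison is biased. It is not. First-treatment pain, painkiller use and satisfaction are self-reported by questionnaire on the shared schedule, and stopping treatment is also covered in patient questionnaires. The exposure is confined to one descriptive table with no test attached.

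4. *Extra visits are extra treatments, and contact is part of a clinic-delivered intervention.* Some excess would therefore be real, and restricting the comparison to common contacts could remove genuine reactions and bias it the other way. This stands against replacing the planned table. It does not rescue that table as the only one, since it cannot separate real excess from extra questioning.

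5. *Tabulation by source belongs in the analysis plan or case report form, which are not shown.* It may well be there, and the article rules out no breakdown. But the point rests on three things the article does state: questioning at each visit, unequal visits, and a by-arm summary of all suspected reactions. If source is not recorded at collection, later analysis may be unable to recover it.

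**Conclusion.** The point holds as a limited one. As written, the summary gives cryotherapy reactions more chances of being recorded, and extra questioning can only raise that arm's reported incidence. Under equal true rates, the illustrated ratio is about 1.04 to 1.27 for reactions after week 2 that precede both extra visits. It is smaller when fewer visits follow the reaction, and 1.00 for patients who need none.

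Those figures rest on assumed per-visit capture of 30% to 80%, assumed self-report capture of 50% to 80% equal in both arms, and independence between contacts. Lower self-report capture would enlarge the ratio. So would poorer recall at week 12 than soon after the event. Positive correlation between visits would shrink it. The direction is firm; the size is uncertain and probably modest. The primary outcome and the sample size are untouched.

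**What to change.** Leave the visit schedule as it is and change the recording and reporting:

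- Add to the adverse event form the source of each event (self-reported or elicited) and the contact at which it was recorded.
- Keep the planned all-source incidence by arm, for safety reporting and as the full count.
- Beside it, show the incidence from contacts common to both arms: the week 2 and week 12 visits and the shared questionnaires. Identify events elicited only at additional cryotherapy visits.
- State in the text that part of any excess at the additional visits may be real reactions to repeat treatment. The restricted table should not replace the all-source one.

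The cost is one data field and one table. The common-contact table will hold fewer events. It may also under-count cryotherapy reactions, because a patient who reported one at an extra visit may not repeat it at week 12. That is why the two tables should be read together.
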